## Background

Cardiovascular diseases (CVD) are the leading cause of mortality and morbidity worldwide and a growing health problem among developing nations [1, 2]. It is argued that metabolic syndrome is the most responsible risk factor for developing the disease [3–6]. The National Cholesterol Education Program Adult Treatment Panel (ATP) III defined metabolic syndrome as the presence of three or more of the following conditions: triglyceride level of at least 150 mg/dl, HDL level less than 40 mg/dl in men and less than 50 mg/dl in women, systolic/diastolic blood pressure 130/85 mm Hg or higher, fasting blood glucose level 110 mg/dl or higher and waist circumference greater than 102 cm in men and greater than 88 cm in women [7]. Metabolic syndrome is affecting about 20% of adult population without known diabetes and cardiovascular diseases and is associated with increasing cardiovascular morbidity and mortality [8, 9]. Ischemic heart disease was the leading cause of Disability-Adjusted Life Years (DALYs) worldwide in 2010 [10].

Recent evidence indicates that individuals with metabolic syndrome are approximately twice more likely to develop cardiovascular disease and between 3.5 and 5 times more likely to develop type 2 diabetes [11]. The prevalence of metabolic syndrome in Iran is very high. The Tehran Lipid and Glucose study (TLGS) reported that 42% of women and 24% of men were suffering from metabolic syndrome. Metabolic syndrome has been identified by central obesity, increased triglycerides, reduced high-density lipoprotein cholesterol (HDL), hypertension, and elevated fasting blood glucose concentration [12–14]. Increased cardiovascular mortality and metabolic syndrome morbidity in developing countries is largely due to the changes in lifestyle including changes in dietary habits and lack of exercise [15–17]. Therefore effective and affordable strategies to control the syndrome would benefit the at risk population.

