### Primary outcomes

The primary outcomes are feasibility, acceptability, usability, and the change in metabolic syndrome components. Measures for assessing feasibility will include: the proportion of participants who respond to log-in to My Healthy Heart Profile for the first time, and response rate to postal follow-up for clinical assessments and complete the study questionnaires [77]. Acceptability will be explored by the number of sign-in to the My Healthy Heart Profile during intervention. Usability of the intervention will be accessed by the educational materials downloads and using of website components by participants. The change in metabolic syndrome components will be assessed by calculating changes in the following measures: waist circumferences, weight, blood pressure, triglycerides, HDL-cholesterol, and fasting blood glucose. Waist circumference will be measured in horizontal plane, midway between the lowest rib and the iliac crest with a measuring tape in centimeter [6]. The weight of individual dressed in light clothing without shoes will be measured at each time using a calibrated scale (Seca model 8811021658). Blood pressure will be measured with mercury sphygmomanometer twice in the same arm after the individual seated at rest 10–15 min. The systolic and diastolic measurement represents the mean of two readings. Blood sampling will be collected for measurements of total cholesterol, triglycerides, LDL-cholesterol, HDL-cholesterol, and fasting blood glucose for all participants. Overnight fasting for 12–14 h is needed before blood sampling. Venous blood samples (5 ml) will be collected. Body Mass Index (BMI) will be measured by individual’s weight divided by the square of the height [78].

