### Sample size

The sample size was calculated based on one standard deviation decrease (2.5) [85] in waist circumference as one of the most important components of MS [86]. As such a study with a power of 90% at 5% significance level would need 60 participants in each arm. Giving that there might be an attrition risk, 80 participants per each group were sought.

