### Statistical analysis

The characteristics of participants will be summarize as proportions or means with standard deviations. To test the study hypotheses t-tests for independent samples will be performed. Comparisons of proportions will be carried out using the Pearson’s chi-square test without continuity correction. For all parameters 95% confidence intervals will be defined. Two-sided p values of less than 0.05 will be regarded as statistical significant. All analyses will be performed with the SPSS software version 18. Between group differences will be evaluated by intent-to-treat analysis using the Generalized Linear Mixed Models (GLMM).

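### Six clinical measures are primary with no lead measure and one flat two-sided 0.05 threshold, and one of them, weight, is not a syndrome component by the protocol's own definition

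*Protocol article*

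**What the plan says.** The Primary outcomes section of the protocol article states: "The primary outcomes are feasibility, acceptability, usability, and the change in metabolic syndrome components". It then assesses the last of these by changes in "waist circumferences, weight, blood pressure, triglycerides, HDL-cholesterol, and fasting blood glucose". Blood pressure is one item in that list but is recorded as two values: "The systolic and diastolic measurement represents the mean of two readings". Follow-up is at 3 and 6 months (Trial design; Secondary outcomes), and neither visit is named as primary.

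The Statistical analysis section sets one threshold for everything: "Two-sided p values of less than 0.05 will be regarded as statistical significant". It gives no ordering, no adjustment and no rule for how many measures must improve. On method it says "To test the study hypotheses t-tests for independent samples will be performed", and it closes by assigning between-group differences to an intent-to-treat analysis with generalized linear mixed models (GLMM).

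The Sample size section bases its calculation on a decrease "in waist circumference as one of the most important components of MS". It does not call waist circumference the deciding outcome.

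The Background describes the syndrome twice. It reports that the ATP III panel "defined metabolic syndrome as the presence of three or more of the following conditions" and lists triglycerides, HDL, blood pressure, fasting glucose and waist circumference. It later says: "Metabolic syndrome has been identified by central obesity, increased triglycerides, reduced high-density lipoprotein cholesterol (HDL), hypertension, and elevated fasting blood glucose concentration". Weight is in neither list.

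**The concern.** The effectiveness part of the primary outcome is a set of separate measures, and the article fixes a significance threshold for each without saying what pattern of results would establish effectiveness. Three things follow.

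- The 5% level applies to each measure and not to the overall conclusion. The error rate of that conclusion depends on a success rule that is not given.
- The measure that was sized and the measures that could decide the trial are not the same set.
- A measure outside the article's own definition of the syndrome is used to assess change in its components. A result on weight alone could therefore be reported as a primary finding about metabolic syndrome.

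**Working it through.** **Inputs from the article.** Six named measures, seven if systolic and diastolic pressure are tested separately (Primary outcomes); two-sided 0.05 for each test (Statistical analysis); two follow-up visits (Trial design). The article gives no correlations between measures or over time, so those below are assumptions.

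**The plan's own figure.** The article states 60 per arm for a decrease of one SD (2.5) in waist circumference at 90% power and 5% significance. The usual formula gives n = 2 × (1.960 + 1.282)² × (2.5/2.5)² = 21.0, so 22 per arm. The stated 60 is not reproduced. At 90% power, 60 per arm corresponds to a standardised difference of (1.960 + 1.282) × √(2/60) = 0.592. This is a separate matter. It affects only the power comparison in the last step, not the error rates.

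**Error rate at one visit.** Suppose the intervention has no effect on any measure and one significant measure is enough. For k independent tests the chance of at least one false positive is 1 − 0.95^k. With correlated tests it is the chance that at least one of k equicorrelated normal statistics exceeds 1.960 in absolute value, found by simulation with 400,000 draws.

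| Assumed correlation | Six measures | Seven measures |
|---|---|---|
| 0 (formula) | 1 − 0.95^6 = 26.5% | 1 − 0.95^7 = 30.2% |
| 0.3 | 24% | 27% |
| 0.5 | 21% | 23% |
| 0.7 | 16% | 18% |

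**Error rate if 3 and 6 months are tested separately.** With 12 or 14 independent tests, 1 − 0.95^12 = 46.0% and 1 − 0.95^14 = 51.2%. Independence is unrealistic for repeated measures in the same people. With correlations of 0.3 to 0.7 between measures and 0.5 to 0.7 over time, the rate is about 26–40% for six measures and 28–44% for seven.

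**Measures against definition.** The five components in the Background are waist circumference (central obesity), triglycerides, HDL, blood pressure and fasting glucose. All five are in the primary list. Weight is the one primary clinical measure with no counterpart.

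**What the remedies cost in power.** A single outcome at two-sided 5% keeps the error rate at 5% with no loss of power. For Holm across five components, the smallest p-value is compared with 0.05/5 = 0.01, so Bonferroni power is a lower bound for each component. With 60 per arm that bound is 99.8% at a one-SD effect. At a 0.592 SD effect it is about 75%, against 90% unadjusted.

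**The case against.** The strongest reply is that the article nowhere says one significant measure would establish effectiveness. The Aim speaks of reducing the indicators in the plural, and the Statistical analysis section sets a threshold, not a success rule. If every component had to improve, there would be no inflation. This stands as a limit on the figures: an any-one-suffices rule is something a reader might infer from the silence, but it is not written. The stricter rule is not written either, so the error rate of the effectiveness claim is left open.

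A reader might also infer that the plan commits to 14 tests and a false-positive risk above one half. The article does not support that. The GLMM can give one group comparison per measure over both visits, blood pressure is listed as one item, and the rate exceeds one half only with 14 fully independent tests. The article also names t-tests and does not say which analysis decides, so separate testing by visit is possible but is only one reading.

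Multiplicity adjustment is often left to an analysis plan that is not shown here. That is fair for technical detail. The choice of primary outcomes, however, is made in this article, and so is the single threshold. The point rests on what is stated.

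Finally, waist circumference alone narrows a plural aim, and the sample size calculation behind it does not reproduce. The first is a real trade-off, so an alternative is given below. The second does not undermine the choice: 60 per arm is more than the 22 that the stated effect requires.

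**Conclusion.** The point holds in a limited form. The article makes six clinical measures primary (seven with separate pressures), names no lead measure or primary time point, and applies one unadjusted threshold.

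If any single measure counts, the chance of at least one false-positive primary result at one visit is 26.5% or 30.2% under independence and about 16–27% at assumed correlations of 0.7 to 0.3, against a nominal 5%. It is higher if both visits are tested separately. That is at least three times the nominal level, but it does not make a chance finding more likely than not at one visit.

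Two parts need no assumption about correlation or success rule: weight is used to assess component change although both of the article's own lists omit it, and only waist circumference was used to size the trial.

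**What to change.** Before outcome data are seen:

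- Name waist circumference at 6 months, from the intent-to-treat GLMM, as the single confirmatory effectiveness outcome at two-sided 5%.
- Make the other four components secondary, with a Holm adjustment or labelled supportive.
- If the sponsor prefers to keep the plural aim, apply Holm across the five components at 6 months as the primary family instead. The text must then say whether blood pressure enters as one variable or as two, since two would make six hypotheses.
- Move weight to the secondary outcomes and treat 3-month values as supportive.
- Report feasibility, acceptability and usability descriptively, outside the confirmatory test. The log-in and profile-use measures exist only in the intervention arm.

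No extra participants or measurements are needed. Under the first option the sponsor gives up claiming effectiveness on whichever measure happens to be significant and accepts a narrower confirmatory objective. Under Holm it keeps the plural aim but loses some power per component: negligible at the stated one-SD effect, and from 90% to no lower than about 75% at the 0.592 SD effect that 60 per arm implies.

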### Secondary outcomes

Secondary outcomes will include assessments of the followings:Health-related quality of life (HRQOL) using the SF-36 (Iranian version). The SF-36 is a very popular measure of health related quality of life among the general population. The psychometric properties of the Iranian version of the questionnaire are well documented [79],Physical activity using the International Physical Activity Questionnaire at last 7 days (IPAQ) [80], a well-validated questionnaire in Iran [81, 82];Food frequency using the validated Iranian version of Food Frequency Questionnaire (FFQ) [83], andPsychological well-being using the Iranian version of 12-item General Health Questionnaire (GHQ-12) [84].

Measurements will be made at baseline (T0), three (T1) and six (T2) months follow-up. Food frequency questionnaire will be completed only on T0 and T2.

### Sample size

The sample size was calculated based on one standard deviation decrease (2.5) [85] in waist circumference as one of the most important components of MS [86]. As such a study with a power of 90% at 5% significance level would need 60 participants in each arm. Giving that there might be an attrition risk, 80 participants per each group were sought.

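### The stated inputs do not give 60 per arm: a one-SD difference at 90% power and two-sided 5% needs 23 per arm, and at 60 per arm its power is 99.97%

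*Protocol article*

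**What the plan says.** In the protocol article, the Sample size section gives the basis as follows: "sample size was calculated based on one standard deviation decrease (2.5) [85] in waist circumference". The next sentence draws the conclusion: "As such a study with a power of 90% at 5% significance level would need 60 participants in each arm". The section then raises the figure to 80 per arm for attrition, without giving a rate.

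The Statistical analysis section supplies the remaining inputs. The test is given by "To test the study hypotheses t-tests for independent samples will be performed", and the threshold by "Two-sided p values of less than 0.05 will be regarded as statistical significant". It also plans an intention-to-treat comparison by generalised linear mixed model and 95% confidence intervals for all parameters. The Randomization section fixes 1:1 allocation.

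The article gives no other SD, and no correlation, multiplicity adjustment or design effect.

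**The concern.** The Sample size section prints an effect, a power, a significance level and a result, and presents the result as the consequence of the other three. An effect of one SD is a large standardised effect, d = 1.0, and the usual two-group calculation then gives a number in the low twenties, far from 60.

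What is at stake is the trial's stated design basis. Waist circumference is one of the metabolic syndrome components listed among the primary outcomes, and it is the only one for which a size calculation is given. If the effect is as stated, 90% is the wrong power for 60 per arm. If 60 per arm and 90% are right, one SD is the wrong effect. As printed, a reader cannot tell which difference the trial was designed to detect.

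**Working it through.** **Inputs**

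- Effect: one SD, printed as 2.5 (Sample size). No unit is given there; the article measures waist in centimetres. Read literally, difference = SD = 2.5, so d = 2.5/2.5 = 1.0.
- Power 90%, significance level 5% (Sample size).
- Two-sided, independent-samples t-test (Statistical analysis).
- 1:1 allocation (Randomization).

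**Attempt to reproduce 60 per arm**

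Normal approximation:

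n per arm = 2 × (z₀.₉₇₅ + z₀.₉₀)² / d² = 2 × (1.960 + 1.282)² / 1.0² = 21.01, so 22 per arm.

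Noncentral t: n = 22.02, so 23 per arm.

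The printed 60 is about 2.7 times the computed requirement (60/22 = 2.7).

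**What 60 per arm delivers**

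- Power for d = 1.0 with 60 per arm (t-test): 99.97%.
- Effect detectable with 90% power and 60 per arm: d = 0.597 (t-test). By the normal approximation, d = 3.242 × √(2/60) = 0.592.
- If the SD is 2.5 cm, this is 0.597 × 2.5 = 1.49 cm.
- If the difference is 2.5 cm, the SD would have to be 2.5/0.597 = 4.19 cm.

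**Other readings tried**

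| Reading (d = 1.0 unless stated) | Result |
|---|---|
| One-sided 5%, 90% power | 18 per arm |
| Two-sided, 95% power | 26 per arm (27 by t-test) |
| One-sample or paired | 13 |
| Nonparametric efficiency correction (22/0.864) | 26 per arm |
| Variance doubled for a change score | 43 per arm (44 by t-test) |
| 60 taken as the total (30 per arm) | 97% power |
| Difference 1, SD 2.5 | 132 per arm (133 by t-test) |

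Two routes do reach 60. One is a doubled change-score variance together with a Bonferroni correction for five tests; neither assumption appears in the article. The other is a difference of 2.5 cm with an SD of about 4.2 cm; then 2.5 is no longer one SD, against the article's own words.

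**Attrition step**

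60/(1 − 0.25) = 80. The step from 60 to 80 is consistent with an allowance of 25% and is not in question.

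**Conditional sensitivity**

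Suppose 2.5 cm was the target difference and the SD is larger than printed. The SDs of 5, 6 and 8 cm are assumptions and do not come from the article.

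| Assumed SD (cm) | d | Power, 60 per arm | Power, 80 per arm |
|---|---|---|---|
| 5 | 0.500 | 78% | 88% |
| 6 | 0.417 | 62% | 75% |
| 8 | 0.313 | 40% | 50% |

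**The case against.** **The error is in the safe direction.** On the only effect and SD that are printed, 23 per arm would do, and the trial plans 60 evaluable and 80 randomised. This stands. A reader might infer from the mismatch that the trial is underpowered; the article does not support that. The lower powers in the sensitivity table require setting aside the words about one SD and assuming an SD that the article does not give. The column for 60 per arm also supposes that the full implied 25% is lost.

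**A null result will be read from its confidence interval.** This also stands. A reader might think that the wrong planning effect would make a null result uninterpretable. The article commits to 95% confidence intervals, and these show which differences the data exclude, whatever effect was used for planning.

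**The figure 2.5 comes from a cited source that is not at hand.** If that source gives a decrease of 2.5 cm and an SD near 4.2 cm, the calculation behind 60 may be sound and only its description wrong. This is possible, but the printed sentence would still need correcting, because 2.5 would not then be one SD.

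**A journal article condenses.** It need not spell out the unit, the SD, or whether the decrease is within or between arms; the planned independent-samples test already points to a between-arm comparison. Such missing detail is therefore not part of the finding. The allowance for condensing does not extend to printed inputs that conflict with the printed answer.

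**Conclusion.** The point holds as an arithmetic inconsistency. With a one-SD between-arm difference, two-sided 5%, 90% power and 1:1 allocation, the requirement is 23 per arm by t-test (22 by normal approximation), against 60 printed. Conversely, 60 per arm gives 99.97% power for one SD, and 90% power for about 0.60 SD.

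This rests on reading the printed effect as the between-arm difference tested by the planned t-test, with difference and SD equal. It needs no figure from outside the article. No reading that the article supports gives 60.

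It does not show a trial that is too small. Whether power falls short of 90% for a 2.5 cm difference depends on whether the SD exceeds about 4.2 cm with 60 per arm, and the article cannot settle that.

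**What to change.** Enrolment stays as planned.

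1. Recover from the full protocol or the cited source the between-arm difference and the SD actually used, and restate the Sample size paragraph with both, so that they reproduce 60 per arm at 90% power and two-sided 5%.
2. If they cannot be recovered, correct the requirement for a one-SD difference to 23 per arm. Then report, labelled as the detectable effect at the chosen size and not as the original basis, that 60 evaluable per arm give 90% power for a between-arm difference of about 0.60 SD (1.5 cm if the SD is 2.5 cm).
3. State the time point to which the difference refers. Assessments are planned at 3 and 6 months and the Sample size section names neither, so the sponsor should specify it; 6 months should not be presumed.

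The cost is a rewritten paragraph and a search for the original inputs. Recruitment, randomisation and analysis are unaffected.

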### Attrition prevention

In order to prevent attrition and encourage people to take part in the study we will use five strategies appropriate to participants. Firstly, free blood testing will be carried out for all participants at all three assessment times. Secondly, the test results will send through e-mail within 24 hours. We will request from users to log-in the personal profile and record the new values. Thirdly, e-mail reminders will send to users when they are inactive for 2 weeks. Fourthly, in order to keep up to date and enhance the website visiting, the new information will be placed on the site monthly. Finally, all recruitment processes will be online.

### Statistical analysis

The characteristics of participants will be summarize as proportions or means with standard deviations. To test the study hypotheses t-tests for independent samples will be performed. Comparisons of proportions will be carried out using the Pearson’s chi-square test without continuity correction. For all parameters 95% confidence intervals will be defined. Two-sided p values of less than 0.05 will be regarded as statistical significant. All analyses will be performed with the SPSS software version 18. Between group differences will be evaluated by intent-to-treat analysis using the Generalized Linear Mixed Models (GLMM).

### Ethics

The ethics committee of the Tehran University of Medical Sciences approved the study protocol. Written informed consent is obtained from all participants.

## Discussion

The Internet is promising medium to offer lifestyle interventions [87]. Perhaps this study will help in refining the intervention for future research and practice. The results from this study, if successful, might help Iranians in several ways. In the first instance it will help to set up similar interventions. Secondly it will help to reach target populations as quickly as possible.

The study by Bosak et al. showed that web-based intervention to increase physical activity in people with metabolic syndrome appears feasible [22]. Recent evidence support that lifestyle interventions including physical activity and low-calorie diet might lead to at least 10% weight loss [88].

Various studies showed a positive association between log-in frequency and weight loss [44]. This approach may also be more persuasive and motivational, with the ability to promote rapid changes in participant’s behavior, but remains to be tested.

